### Intervention

The *Drinks*:Ration app, formerly called *InDEx* [49-51], has been developed following the Medical Research Council Complex Intervention Guidelines and using co-design methodology. It has been developed by the King’s Centre for Military Health Research (at King’s College London) and the University of Liverpool, supported by experts in smartphone app development, epidemiology, addiction psychiatry, and military mental health. The app is designed to support veterans drinking at a hazardous or harmful level by providing bespoke advice and support over a 28-day period. The app is designed to enhance participants’ motivation and self-efficacy in modifying their alcohol consumption by means of BCT in the content displayed (Multimedia Appendix 1) and the messaging sent to participants. The iterative development process, theoretical framework, and feasibility trial have already been reported [49-51]. Briefly, *Drinks*:Ration has been developed and tested with the following 5 core modules:

Account management: participants can modify personal information (eg, first name and mobile number) and app parameters (eg, automatic logout, clear local storage, data-sharing permission, and exiting the study).Questionnaire and individualized normative feedback: it captures the participant’s responses to a set of questions and aggregates responses to produce an individualized infographic that represent the participant’s alcohol consumption compared with the general population, the AF Community, and other participants of *Drinks*:Ration.Self-monitoring and feedback: it records alcohol consumption by participants and provides a range of visual illustrations (eg, charts, figures, and texts) to allow for monitoring of alcohol consumption. Moreover, the participants can select visual metrics relevant to their interest (eg, calories, cost, and exercise required).Goals (setting and review): participants can set goal(s) based on the implementation intentions (if and then) [52] methodology; visual feedback provides feedback on progress toward achieving set goal(s).Personalized messaging: participants are sent tailored messages via push notification or SMS text messaging that provides prompts to use the drinks diary, suggests alternative behaviors, and provides feedback on set goals.

The app is compatible with all modern iOS- and Android-supported devices, and no involvement of the research team is required for participant enrolment. Data is collected, managed, and processed using the Google Firebase server infrastructure in London, United Kingdom.

In this study, the intervention arm will receive the app with all functionalities, including push notifications and SMS text messaging. The control arm participants will have access to only the *questionnaire and feedback* module and will not receive any form of personalized messaging, except prompts to complete questionnaires and reminders to review alcohol consumption feedback (see the Message section for more information). Participants in both arms will complete additional questionnaires on their mood and general mental health when responding to the weekly questionnaires. These responses will be used to personalize the content of the app and push notifications and SMS text messaging delivered to the intervention arm only.

Participants in both arms will be asked to use the app for 28 days. After which, they can continue to use the app; however, they will not receive personalized messaging, and the data collected after this point will not be used in the analyses. However, participants will receive a reminder message on day 84 and day 168 to complete questionnaires.

### Messaging: Push Notifications and SMS Text Messaging

In addition to the *Drinks*:Ration app, participants will receive personalized push notifications and SMS text messaging that provide prompts to use the drinks diary, complete questionnaires, suggest alternative behaviors, provide feedback on goals, and promote a healthy lifestyle. A bank of personalized messages (both for SMS text messages and push notifications) informed by 180 tailored messages developed previously (which are informed by the Health Action Process Approach framework and targeted toward specific BCTs) [49] will be used.

*Drinks*:Ration uses baseline and contiguous measurements (day 7/14/21) to inform the type of message a participant receives to provide an individual participant-centric approach. Baseline measurements are used to identify suitable messages, *and as a participant engages with Drinks*:Ration, continuous measurements, including questionnaires (baseline and weekly questionnaires) and the drinks diary, are used to reflect current behavior and attitude. The messages cover a wide range of topics to target beliefs and motivations, with the primary aim of increasing the participant’s awareness of their drinking habits and behaviors. The messages are divided into 3 categories:

Tailored: personalized to drinking habits, baseline, and weekly questionnaires;Tailored and triggered: tailored to baseline and contiguous measurements and a specific event occurring; andTargeted (generic): sent on specific days to highlight inactivity, as a reminder to complete a questionnaire, or to alter participants to a new feature.

A participant can receive a maximum of 20 messages over the 28-day period, with a maximum of 2 messages in a single day. The system automatically decides when a message should be sent and the mode of delivery (push notification or SMS text messaging). A list of targeted (generic) messages to be sent to participants is defined in Table 1; except the messages listed in this table, participants in the control arm will receive no other messages. Participants in both arms will receive a generic message designed to promote retention of the *Drinks*:Ration app to allow for follow-up data collection. This will be sent monthly.

**Table 1 table1:** A list of targeted (generic) messages and the day on which they are sent.

Day	Message content	Study arm
0	Title: Welcome to *Drinks*:Ration Message: Your signup is complete. Remember to log last week’s alcohol consumption	Intervention
0	Title: Welcome to *Drinks*:Ration Message: Your signup is now complete	Control
2	Title: Time to set a goal? Message: Why not set a goal to reduce the amount you drink? You can start now by clicking on the *goals* tab in the app…	Intervention
7	Title: Drinking Advice Message: Remember to open *Drinks*:Ration for advice on how to make your alcohol consumption	Control
13	Title: Remember the diary Message: Completing the drinks diary each day allows you to see how well you are doing!	Intervention
14	Title: Let us know… Message: Remember to open the app to tell us how you’re doing	Intervention and control
18	Title: Remember to monitor Message: Monitoring what you drink is proven to help you cut down—why not start fresh this week?	Intervention
21	Title: Be aware! Message: It is good to be aware of what you drink. Monitoring your alcohol consumption really can help your health!	Intervention and control
23	Title: Think… Message: Using Drinks:Ration may have changed some of the drinks you usually have. Try and think how you can keep it up!	Intervention
28	Title: Let us know… Message: Please let us know how you’re getting on!	Intervention and control
56	Title: Keep checking in… Message: Please remember to open the Drinks:Ration app	Intervention and control
84	Title: Let us know… Message: Please let us know how you’re getting on!	Intervention and control
112/140	Title: Keep checking in… Message: Please remember to open the Drinks:Ration app	Intervention and control
168	Title: Let us know… Message: Please let us know how you’re getting on!	Intervention and control

### Measures

A summary of the measures and data collection timepoints in this study are detailed in Table 2.

#### Baseline Measures

Upon successful registration, participants will complete a baseline questionnaire to assess physical and mental health, health status, resource utilization (eg, visits to hospital because of alcohol, and days in hospital because of alcohol), and sociodemographics (eg, age, gender, ethnicity, employment status, and occupation).

**Table 2 table2:** Summary of measures and data collection timepoints.

Day or measure		0		7		14		21		28		84		168	
**Questionnaires (Multimedia Appendix 2)**															
	Informed consents		I^a^/C^b^		—^c^		—		—		—		—		—
	Sociodemographic		I/C		—		—		—		—		—		—
	Resource utilization		I/C		—		—		—		I/C		I/C		I/C
	Depression (PHQ2^d^) [53]		I/C		I/C		I/C		I/C		I/C		I/C		I/C
	Anxiety (GAD2^e^) [54]		I/C		I/C		I/C		I/C		I/C		I/C		I/C
	International Trauma Questionnaire for PTSD^f^ [55]		I/C		—		—		—		I/C		I/C		I/C
	Readiness to Change Ruler [56]		I/C		—		—		—		I/C		I/C		I/C
	Self-Efficacy Ruler [56]		I/C		—		—		—		I/C		I/C		I/C
	Alcohol Use Disorder Identification Test [57]		I/C		—		—		—		I/C		I/C		I/C
	World Health Organization Quality of Life-BREF [58]		I/C		—		—		—		I/C		I/C		I/C
	7-day Timeline Follow-Back for alcohol consumption [43]		I/C		—		—		—		I/C		I/C		I/C
**Usability evaluation**															
	Qualitative interviews^g^		—		—		—		—		I/C		—		—
	mHealth App Usability Questionnaire [59]		—		—		—		—		I/C		—		—
**Remote data collection**															
	Wearable sensors^h^		I/C		I/C		I/C		I/C		I/C		I/C		I/C
	Smartphone sensors^h^		I/C		I/C		I/C		I/C		I/C		I/C		I/C

^a^I: Intervention arm.

^b^C: Control arm.

^c^—: no data is collected during this period.

^d^PHQ2: Patient Health Questionnaire 2-item.

^e^GAD2: Generalized Anxiety Questionnaire 2-item.

^f^PTSD: posttraumatic stress disorder.

^g^20 participants will be invited to participate in a qualitative interview.

^h^Additional participant consent required.

#### Outcome Measures

The primary outcome measure is the change between self-reported alcohol consumption as measured by the 7-day TLFB [43] over the previous 7 days between baseline (day 0) and 3-month follow-up (day 84). Participants will be asked to report how many drinks they consumed over the last 7 days as well as the type of drink they consumed on each day. Using the standard unit of measurements (Multimedia Appendix 3), weekly alcohol consumption will be determined by summing the number of units assigned to each drink. The TLFB has been extensively used to assess alcohol consumption and has demonstrated good test-retest reliability [43,60]. Secondary outcome measures will be (1) change in the baseline to follow-up AUDIT score and (2) change in the baseline to follow-up World Health Organization Quality of Life-BREF (WHOQOL-BREF) score to assess quality of adjusted life years. Process evaluation measures, following the model by Donabedian for evaluating quality of care [61], will be (1) app use (number of app engagement, screen views, and user retention) and (2) usability ratings as measured by the mHealth App Usability Questionnaire (MAUQ) [59]. A 3-month follow-up period was selected to assess the short-term benefits of the intervention on participants. The primary and secondary outcomes will also be reassessed at 6-month follow-up (day 168) to assess the longer term benefits of the intervention and will be reported as a secondary outcome.

### Study Debrief

At the end of the follow-up period, a random selection of 20 participants (10 from each study arm) will be invited to take part in a 60-min *debrief* session. The aim of this is to understand more about their use and experience of the *Drinks*:Ration app. During the session, participants will be asked to share their views on acceptability and usability and what can be done to improve their experiences. This will be done via telephone and transcript generated and used for analysis. Participants taking part in the debrief session will have the opportunity to view and discuss their own data.

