For process evaluation measures, app utilization will be assessed using descriptive statistics of frequency of engagement using a previously published procedure [62]. This will include the number of times the app is initialized (started when not running in the background), the average session duration (time spent using the app overall and for each page), the number of times a participant performs an interaction (synchronize data, add a drink, or add a message rating), and the number of weeks in which participants remain engaged with the app. Participant engagement is defined as having at least 3 interactions in a 7-day period, other than receiving push notifications or SMS text messages, and will be used as a proxy for usability. An independent sample analysis will be carried out to explore and identify differences between the intervention and control arms. Usability of *Drinks*:Ration will also be reported using descriptive statistics and thematic analysis of *debrief* sessions. Finally, analyses will be carried out to identify differences between the intervention and control arms in app experience (as measured by MAUQ). In the pursuit of open science, data and code syntax will be published alongside reporting of the trial. As this is a single-blinded RCT, an independent researcher (who will be blinded to allocation) will review all analyses and data before publication. This study will be reported following the Template for Intervention Description and Replication [63] and CONSORT (Consolidated Standards of Reporting Trials) checklist [64].

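### Table 2 schedules the qualitative interviews at day 28, before the day-84 primary outcome, while the Study Debrief section places what appears to be the same session at the end of follow-up

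*Protocol article*

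**What the plan says.** The Study Debrief section gives the time and size of the session: "At the end of the follow-up period, a random selection of 20 participants (10 from each study arm) will be invited". The same section sets its length at 60 minutes and its mode as telephone. It gives the aim as learning about use and experience of the app, and adds: "Participants taking part in the debrief session will have the opportunity to view and discuss their own data".

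Table 2 gives a different time. Its columns are days 0, 7, 14, 21, 28, 84 and 168. Under the usability evaluation heading, the row for qualitative interviews is marked for both arms at day 28 only. Every other cell holds a dash, which the table footnote defines as "no data is collected during this period". Another footnote gives the number: "20 participants will be invited to participate in a qualitative interview".

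The Statistical and Data Analysis Plan says that usability "will also be reported using descriptive statistics and thematic analysis of *debrief* sessions". It mentions no other set of interviews.

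**The concern.** A schedule table is what a study team tends to work from. If this one is followed, a random subset of both arms has up to an hour's conversation with a researcher, with the chance to review their own data, before the primary outcome is collected. The outcome is self-reported drinking, which such a conversation could plausibly influence, and the two arms might respond differently because one has had the full app and the other has not. A discussion of which features a person used could also show the interviewer, and possibly the participant, which arm that person was in.

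A session at that point would also sit badly with two other statements. Study Design describes a trial that runs through the platform without the research team taking part. Follow-Up Procedure and Data Monitoring says the team makes no contact beyond the app's automatic messages unless the participant approaches it first.

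**Working it through.** The plan gives no figure of its own to reproduce here. The check is a comparison of passages plus simple arithmetic for scale.

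**1. Reading the table row.** There are seven column headings and seven cells in the interview row: dash, dash, dash, dash, I/C, dash, dash. The filled cell is the fifth, and the fifth heading is day 28. Headings and cells match in number, so the placement does not look like a fault of text extraction.

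**2. Reading the text.** Outcome Measures uses follow-up for day 84 (3 months) and day 168 (6 months). The Intervention section describes day 28 as the end of the requested app use. Study Debrief does not say which follow-up it means, but neither reading gives day 28.

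**3. Is it one session?** Table 2 speaks of a qualitative interview and the text of a debrief.

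| Feature | Table 2 and footnote | Study Debrief and analysis plan |
|---|---|---|
| Number invited | 20 | 20 (10 per arm) |
| Arms | both | both |
| Purpose | usability evaluation | acceptability and usability |
| Length, viewing of own data | not stated | 60 minutes, yes |
| Time | day 28 | end of follow-up |

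Number, arms and purpose agree, and no second set is described. Identity is therefore a reasonable inference, but the document does not state it.

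**4. Distance to the outcomes if the table is followed.**
- To the primary outcome: 84 − 28 = 56 days.
- To the last follow-up: 168 − 28 = 140 days.

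**5. Share of the sample.** The inputs are in the sample size paragraph at the end of Exclusion Criteria: 37 per arm, 620 invited, 30% acceptance, 40% attrition.
- Required sample: 2 × 37 = 74, and 20 / 74 = 27%. Per arm, 10 / 37 = 27%.
- Implied completers: 620 × 0.30 = 186 enrolled, and 186 × (1 − 0.40) = 111.6, about 112. Then 20 / 112 = 18%.

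Both shares are upper limits. They assume that all 20 invited people accept and that all are among those analysed.

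**The case against.** The strongest reply is that the harm arises only by combining two sources. The hour's length and the viewing of own data are stated only in Study Debrief, the same section that puts the session at the end of follow-up. Table 2 says no more than that an interview takes place. If the text governs, nothing happens before day 84 and the table holds a misplaced entry. This stands. The text is the more detailed description, so a slip in the table is at least as likely as a planned day-28 session. The effect on the trial must therefore be put conditionally.

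A reader might go further and infer three things that the document does not support.

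- **That the session gives controls the feedback their app is designed to withhold.** Controls already receive feedback on their baseline drinking, with reminders to consult it (Study Design; Intervention). What they lack are elements such as the diary, interactive feedback and goal setting. Study Debrief speaks of participants' own data, not specifically of drinking data, and offers only an opportunity to view it.
- **That the session breaks the blind.** No passage says that the arm is disclosed or who conducts the interview, and Randomization and Blinding already exempts one team member from blinding. The primary outcome is reported through the app, so an interviewer's knowledge would not enter its measurement directly. Disclosure is possible but not established.
- **That a specific loss of power follows.** The protocol states no standard deviation and nothing about how far such a conversation would change drinking. Any power figure would rest on assumptions about both, and on how many interviewees accept and complete. None can be taken from the document.

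It can also be said that Study Debrief names no day, and that Outcome Measures speaks of a 3-month follow-up period, so day 84 may be what was meant. This too stands. Day 168 is a recommendation of this review and not something the text already says.

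**Conclusion.** The contradiction holds: day 28 in Table 2 against the end of follow-up in Study Debrief. It rests on treating the interview and the debrief as one session, which the matching number, arms and purpose support.

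It is more than a clerical matter. Executing the table as printed would place researcher contact ahead of the self-reported primary outcome in up to 20 participants (27% of the required sample, about 18% of the implied completers), contrary to the hands-off conduct described elsewhere. Co-intervention and disclosure of allocation would then be possible. The size and direction of any bias cannot be computed from the document. If the Study Debrief text is followed, the day-84 outcome is not exposed. Whether the day-168 outcome is also protected depends on which follow-up that section means.

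**What to change.** Correct the interview entry in Table 2 so that it agrees with Study Debrief. In both places, state that the session is held only after the participant's last TLFB assessment, that is, after the day-168 questionnaire. This resolves the unnamed day in Study Debrief and protects both the day-84 and the day-168 outcomes. Use one name for the session in the table, the text and the analysis plan, so that its identity no longer has to be inferred. Leave the mHealth App Usability Questionnaire at day 28.

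The change is one table entry and a short clause in the text. The only real cost is that the interviewees would recall the app about 140 days after the requested use ended. The day-28 questionnaire still captures the earlier experience.

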### Study Withdrawal and Consent

Informed consent will be sought from all participants via the *Drinks*:Ration app before the collection of any personal data, and they will be informed from the outset that they can withdraw from the study at any time. Individual optional consent (screenshots presented in Figure 2) will be sought for access to the GPS location, sending of push notifications, or SMS text messaging. In addition, to promote open science, consent will be sought from participants to share their data anonymously for research purposes. These data will be released upon completion of the study. Only the questionnaire response, remote measurement technology data, and alcohol consumption statistics will be shared. All data will be deidentified, and no personal data will be released. Participants can change optional consents at any time via the *settings* page of the app until analyses are performed at which point data will be extracted and analyzed.

**Figure 2 figure2:**
[figure not shown]
Consent flow screenshot examples presented to all participants of the study.

Participants can withdraw from the study at any time within the *Drinks*:Ration app (Figure 3). Participants can choose to withdraw from the study but allow the research team to use the data or delete their account by contacting the research team. We anticipate several reasons for withdrawal from the study, such as:

Participant choosing to no longer take part in the study: participants will be informed via the *Drinks*:Ration app that participation is voluntary and that they can withdraw from the study at any point without providing a reason.Adverse event: participants may be withdrawn by the research team in the event of an adverse event, protocol violation, technical, administrative, or other reason(s).

**Figure 3 figure3:**
[figure not shown]
Participant withdrawal screen with includes the ability to delete account or withdraw from the study.

In the event that participants choose to withdraw from the study, we will provide prompt for a reason as to why they are withdrawing; however, providing a reason will be optional. Participants will be asked to uninstall the *Drinks*:Ration app. All data, including those from withdrawn participants, except the anticipated rare request for their data to be deleted, will be included in the final analysis.

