### Study Design

This is a two-arm participant-blinded (single-blinded) RCT, which compares a smartphone app (control arm) that includes feedback on baseline self-reported alcohol consumption with a smartphone app (intervention arm) that includes individualized normative feedback, in addition to features designed to enhance participants’ motivation, app interactive feedback, and self-efficacy in modifying their alcohol consumption. We hypothesize that the intervention arm app will be efficacious in reducing alcohol consumption compared with the control arm app. In this study, both the control and intervention arms will be delivered via one smartphone app known as *Drinks*:Ration. Participants in the control arm are given access only to the alcohol consumption feedback on the basis of publicly available health guidance [42] and reminder messaging to consult the feedback. Those in the intervention arm are given full access to the app, which includes all theoretically driven components and messaging (discussed further in the Intervention section). Both arms will be asked to use the app for 28 days. This study is designed such that the control arm structurally resembles the intervention arm but lacks the active ingredients (eg, drinks diary, interactive drinking feedback, and goal setting). This approach was selected to ensure (1) that both groups receive a digital intervention, (2) uniformity and provide relevance to real-world interventions, and (3) that participants are blinded from the study arm they are assigned to. The trial is conducted via the *Drinks*:Ration platform without any need for involvement of the research team, including the collection of informed consent and data collection. The study flow and data collection points are shown in Figure 1.

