### Follow-Up Procedure and Data Monitoring

The research team will monitor incoming data to ensure that the app is functioning correctly. The research team will not contact participants outside automatic messaging of the app unless they reach out to the research team with queries, for example technical issues, or if they are unsure of how to perform a task with the app.

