### Statistical and Data Analysis Plan

Statistical analysis will be performed after completing the data-collection phase. No interim analysis will be undertaken. The threshold for statistical significance will be *P*=.05, and effect sizes will be reported. Descriptive statistics (eg, demographics and response rate) and independent sample *t* tests and chi-square tests will be carried out to explore and identify potential differences between the intervention and control arms at follow-up. An intention-to-treat method will be used for primary outcome analysis such that those who are lost to follow-up will be retained in the primary analysis. Multiple imputation will be performed to estimate missing data, where appropriate. The primary outcome analysis will examine whether there is a statistically significant difference between the intervention and control arms on change in self-reported TLFB UK units consumed (as stated earlier, a difference of 4 UK units will be considered meaningful). Repeated-measures mixed modeling analyses will be conducted to examine the primary hypothesis that those who receive the full functionality of *Drinks*:Ration will report a greater reduction in alcohol consumption compared with control participants from baseline to 3-month follow-up (day 84). For the secondary outcomes, changes in the AUDIT score and WHOQOL-BREF computed quality of adjusted life years will be assessed using repeated-measures mixed modeling. These analyses will be repeated to assess changes between baseline and 6-month follow-up and will serve as a secondary outcome to assess the longer-term impact of the intervention on participants. These analyses will be reported as secondary outcomes.

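### At the point of withdrawal the protocol does not separate stopping the app from leaving follow-up, so a formal withdrawal before day 84 leaves the primary outcome to be imputed

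*Protocol article*

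**What the plan says.** Under Study Withdrawal and Consent, the choices are set out as follows: "Participants can choose to withdraw from the study but allow the research team to use the data or delete their account". The Figure 3 caption describes the screen in the same terms, as including "the ability to delete account or withdraw from the study". The uninstall request comes in the paragraph that opens "In the event that participants choose to withdraw from the study", and reads "Participants will be asked to uninstall the" app. The same paragraph keeps withdrawn participants' data in the final analysis unless they ask for deletion.

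Three other sections establish how outcomes are collected:

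- Study Design: the trial runs on the Drinks:Ration "platform without any need for involvement of the research team, including the collection of informed consent and data collection".
- Messaging: a monthly generic message goes to both arms to encourage them to keep the "app to allow for follow-up data collection".
- Follow-Up Procedure and Data Monitoring: "The research team will not contact participants outside automatic messaging of the app", apart from answering queries that participants raise. The Adverse Events section adds contact for safety only.

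The Statistical and Data Analysis Plan states that "those who are lost to follow-up will be retained in the primary analysis", with multiple imputation where appropriate.

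**The concern.** The intervention lasts 28 days and the primary endpoint is at day 84, so the last 56 days before the endpoint serve only to measure the outcome. Someone who has had enough of the intervention could still supply a day-84 drinking report. At the moment of withdrawal, however, no such choice is described, and the participant is asked to remove the only instrument that could collect it.

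The arms also differ in what there is to tire of. The diary, goal setting and personalized messages belong to the intervention arm; the control arm has the questionnaire and feedback module and the generic messages that Table 1 marks for it. Withdrawal could therefore be more frequent in one arm and related to drinking. Imputation from observed data cannot be relied on to correct that kind of missingness.

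**Working it through.** **Step 1. Trace a participant through the text.**

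| Participant's action | What the protocol provides | Day-84 outcome |
|---|---|---|
| Stops using the app, does not withdraw | Stays enrolled; questionnaire reminders on days 84 and 168 (Intervention; Table 1) | Can be observed |
| Switches off messages in settings | Optional consent, changeable at any time (Study Withdrawal and Consent) | Can be observed in the app; whether the day-84 reminder also stops is not stated |
| Withdraws from the study before day 84 | Data already held are kept; asked to uninstall | No route described; imputed |
| Deletes the account | Data may be removed on request | None |

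Only the third row is at issue.

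**Step 2. What imputation would have to work with.** Table 2 schedules the 7-day TLFB on days 0, 28, 84 and 168. A withdrawal before day 28 leaves only the baseline TLFB. A withdrawal between days 28 and 84 leaves at most two readings.

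**Step 3. The plan's own figures.** Study Sample gives 37 per arm (74 in total), 30% acceptance, 40% attrition and at least 620 invitations. With 40% lost, the invitations needed are 74 / 0.6 / 0.3 = 411, which does not reproduce 620. With 40% retained, 74 / 0.4 / 0.3 = 617, which does. That discrepancy is a separate matter, but it means the expected loss could be read as 40% or 60%, so both are shown. Acceptances: 620 × 0.30 = 186, or 93 per arm.

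**Step 4. How many outcomes could be involved.** Let q be the share of losses that are formal withdrawals. The documents do not give q; 10%, 25% and 50% are assumptions. Outcomes recoverable = 186 × loss × q. Remaining missingness = loss × (1 − q). Both suppose that every withdrawer would answer, so they are upper limits on the gain.

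| Loss | Missing of 186 | Recoverable at q = 10% / 25% / 50% | Missingness left |
|---|---|---|---|
| 40% | 74.4 | 7.4 / 18.6 / 37.2 | 36% / 30% / 20% |
| 60% | 111.6 | 11.2 / 27.9 / 55.8 | 54% / 45% / 30% |

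**Step 5. Illustrative bias.** If withdrawers make up a fraction w of an arm and their true values differ from the imputed ones by d units on average, that arm's mean is off by w × d. The error in the treatment difference is w_I × d_I − w_C × d_C, with I for intervention and C for control. Suppose, purely for scale, that d = 4 units in the intervention arm (the size of the target difference) and d = 0 in the control arm. At 40% loss, w = 0.40 × q = 0.04, 0.10 or 0.20, so the error is 0.16, 0.4 or 0.8 units. At 60% loss, w = 0.06, 0.15 or 0.30, so the error is 0.24, 0.6 or 1.2 units. If w and d are equal in the two arms, the error is zero.

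**Step 6. Why power is not the measure.** The SD is not stated. Back-solving from 37 per arm, 80% power and a two-sided 5% test gives SD = 4 × √(37/2) / (1.960 + 0.842) = 6.14. At that SD, the roughly 112 observed participants left after 40% attrition (186 × 0.6) give about 93% power. If 60% are lost, about 74 remain and power is 80%. Neither figure says how many losses are formal withdrawals.

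**The case against.** The strongest reply is that the uninstall request applies to leaving the study, and that ending data collection when someone leaves a study is normal practice. App use is only requested for 28 days and is optional afterwards. Personalized messaging stops at day 28, messages are an optional consent, and inactivity is met with reminders, not removal. All of this stands. A reader might infer that stopping the intervention automatically costs the primary outcome, or that a participant tired of messages has no way to stay in. The documents do not support either reading.

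Nor is there a contradiction with intention-to-treat. Withdrawn participants' existing data are used, and those lost to follow-up stay in the analysis through imputation. Retaining someone in the analysis is compatible with not having observed their outcome, though it is a weaker position than observing it.

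A third point stands in part. Figure 3 is not visible, its caption need not list every option, and the article condenses a fuller protocol that might describe another route. But the article itself specifies the exits and the uninstall step, so the point rests on stated text and not on silence alone.

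That withdrawals will be unequal between arms is plausible from the difference in content, but no figure in the document shows it.

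**Conclusion.** The point holds in a narrow form. On the text shown, a participant who formally withdraws before day 84 is asked to remove the only described outcome route, and is offered no explicit choice to leave the app while staying in follow-up. Their primary outcome can then only be imputed.

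The size cannot be fixed from the document, because the share of attrition that is formal withdrawal is not given. Under the assumed shares, between about 7 and 37 of 186 outcomes are involved at 40% attrition, and the illustrative bias runs from 0.16 to 0.8 units against a target of 4. A reader might want to express this as lost power. The documents do not support that, since it would need both an SD and a withdrawal rate that they do not state.

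A neighbouring route deserves notice. The team may withdraw participants after an adverse event, which can be reported through a drinks diary that the control arm lacks, and only data collected before withdrawal are mentioned for them. Such loss could relate to the outcome and differ by arm. The uninstall sentence itself covers only participants who choose to withdraw, and no view is taken here on when the team should withdraw anyone.

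This is a design weakness that is cheap to reduce, not an error that invalidates the analysis.

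**What to change.** - Add a choice to the withdrawal screen, shown before any uninstall request: stop app content and messages, but still answer the day-84 and day-168 questionnaires. This could be a questionnaire-only mode in the app, or an SMS or web link to the mobile number that eligibility already requires. Because SMS is an optional consent, the choice needs its own consent sentence.
- Ask only those who decline all follow-up to uninstall. Leave full withdrawal and account deletion available without conditions.
- State that outcomes given after stopping the app are analyzed in the arm as randomized, and report the number choosing each exit by arm.

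The cost is one screen option, a questionnaire link and a consent sentence, with no extra visits. The downside is a possible second mode of questionnaire completion if a web link is used; the mode should be recorded so that it can be described.
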